## Abstract

**Background:**

In 2012, nearly 4000 children in Malaysia were referred to hospital pediatric dental services due to dental caries. Recent research has reported the effectiveness of dental home visits in preventing caries development in young children. Dental home visits (DHVs) are described as an ongoing relationship between the dentist and their patients, providing all aspects of a preventive oral health care program in the presence of the parents at home.

**Objective:**

The objective of this study is to evaluate the cost-effectiveness of dental home visits and oral health information, in the form of educational leaflets, in preventing new caries development in young children, compared to those receiving only educational leaflets over a period of two years. Cost-effectiveness analysis will be used to evaluate the cost-effectiveness of dental home visits.

**Methods:**

This is a collaborative project with the Oral Health Division of the Ministry of Health Malaysia. The Oral Health Division will provide access to a subsample from the National Oral Health of Preschoolers Survey which was carried out in 2015. The population of interest is children aged 5 and 6 years from kindergartens in the Selangor state of Malaysia. The study adopted a societal perspective for cost-effectiveness analysis and all types of resources that are of value to society will be included in analyzing the costs; such as cost to the patient, cost to the provider or institution, and indirect costs because of loss of productivity.

**Results:**

The trial has been approved by the International Medical University Malaysia’s Joint Research and Ethics Committee (Project ID: IMU R157-2014 [File III – 2016]). This trial is currently recruiting participants.

**Conclusions:**

The number of young children in Malaysia who have been referred to the hospital children’s dentistry service for severe caries is disturbing. The cost of dental treatment in young children is high due to the severity of the caries which require an aggressive treatment, and the need for general anesthesia or sedation. This study will provide information on the cost and effectiveness of DHVs in caries prevention of young children in Malaysia.

**Registered Report Identifier:**

RR1-10.2196/10053

## Introduction

In Malaysia, 86% of rural and 69% of urban preschool children have experienced dental caries, most of which remain untreated [1]. The dental treatment cost in young children is high due to the need for treatment under general anesthesia or sedation, therefore causing significant economic and social burdens on the families [2,3]. In 2012, nearly 4000 children in Malaysia were referred to hospital pediatric dental services because of dental caries [4].

Recent research has reported the effectiveness of dental home visits (DHVs) in preventing the development of caries in young children. The American Academy of Pediatric Dentistry describes DHVs as an ongoing relationship between the dentist and their patient, providing all aspects of a preventive oral health care program in the presence of the parents at home [5,6]_._ This concept has been reported to result in a sustainable oral health behavioral change as the child is more likely to receive appropriate preventive and routine oral health care, thereby reducing the risk of preventable dental disease [7]. In addition, DHVs have the advantage of providing a personalized preventive intervention based on a child’s needs [8].

A study reported in 2013 by Plonka et al showed that oral health education for children through home visits significantly reduced the rate of development of early childhood caries (ECC) compared to those who were contacted via telephone [9]. The results of this study showed the benefit of personal contact in home visits for delivery of oral health education, and this significantly reduced the number of children who developed ECC [9].

Other studies have investigated the cost-effectiveness of DHVs in caries prevention. One such example is a study which investigated the benefit-cost and cost-effectiveness of a long term dental health program for prevention of ECC in infants through home visits, and this study showed favorable results [10]. In a separate study, a home-visit intervention for ECC was found to be more cost-effective than a telephone intervention delivery mode, contributing significant cost savings to the public health care system [11].

Educational leaflets (ELs) are one of the materials commonly used in oral health promotion programs, which reinforce oral health education messages and are frequently used for the benefit of dental patients to complement communication with the dentist [12,13].

Cost-effectiveness analysis (CEA) is widely used to inform decision-makers about the value of new health programs and interventions. CEA is the most commonly used technique for economic evaluation and it estimates the costs and effects of health interventions and sums up the results in a cost-effectiveness ratio [14].

Given the high prevalence of dental caries in Malaysia, and the availability of effective DHVs and ELs material to support oral health promotion, the rationale of this study is to identify effective and cost-effective behavioral interventions to promote oral health and reduce oral health disparities in the population [1,7,8,12,13]. Health behaviors and lifestyles can influence both the oral and general long-term health of the population which can have economic and social consequences [15]. Furthermore, this is the first reported study of DHVs in Malaysia and an economic evaluation in this area is needed to estimate the value of the outcomes received for the expenditures spent on this intervention.

The aim of this study is to evaluate the cost-effectiveness of DHVs and oral health information in the form of ELs in preventing new caries development in young children, compared to those receiving only ELs over a period of 2 years. The specific objectives are:

To determine the cost of DHVs and ELs for prevention of new caries per child compared to the cost for a child only receiving oral health information through ELs for prevention of new caries after a 2-year follow-up.To determine the cost of DHVs and ELs in improving the oral health-related quality of life (OHRQoL) for one child compared to the cost of only ELs in improving the OHRQoL for one child after a 2-year follow-up.To compare the cost of dental treatment incurred and all associated expenditures among children receiving DHVs and ELs and those receiving only ELs over 2 years.

## Methods

### Study Design

This is a CEA of DHVs to families of young children for caries prevention compared to young children receiving oral health information in the form of ELs over a period of two years. For the CEA, the study adopted a societal perspective, which has been suggested as the most appropriate and comprehensive perspective [14]. In this perspective, all types of resources that are of value to society will be included in analyzing the costs; such as cost to the patient, cost to the provider or institution, and indirect costs because of loss of productivity.

### Ethics, Consent, and Permission

Ethics approval for this project will be obtained from the International Medical University Malaysia’s Joint Research and Ethics Committee. Approval for cooperation from the selected kindergartens will be obtained from the Ministry of Education of Malaysia.

### Recruitment

This is a collaborative project with the Oral Health Division (OHD) of the Ministry of Health Malaysia. The OHD will provide access to a subsample population from the National Oral Health of Preschoolers Survey (NOHPS) which was carried out in 2015. The population of interest is children aged 5 and 6 years from kindergartens in the Selangor state in Malaysia. The names and addresses of the kindergartens will be obtained from the OHD.

Upon obtaining an appointment, the researchers will visit the selected kindergartens to provide details about project to the heads of the kindergartens and determine their interest in participating in the study. The heads will be asked to distribute the information leaflets and consent forms to all 5- and 6-year old children in the kindergarten to be taken home to their parents. The information leaflet will include details about the study as wells as the researchers’ names and telephone numbers for any further enquiries. Parents will be given a week to read the information leaflet and to allow parents time to make any enquiries necessary before giving consent. The parents who agree to participate in the study will be asked to sign the consent form and provide their phone numbers, addresses, and children’s names for future contact. The forms will be returned to the kindergarten. Participants in this study will be identified from the consenting families and only children aged 5 or 6 years at commencement of the study will be eligible for inclusion.

### Sample Size and Randomization

It is estimated that there will be a 5% of incidence of caries in the intervention group during the follow-up, compared with 20% in the control group. This is based on the findings of a study conducted in 2015 by Koh et al that reported a 4% of incidence of caries in the intervention group and 39% in the control group [11]. Using a statistical software, Epi info 7 (Center for Disease Control and Prevention, USA, 2015), a sample size calculation was conducted and a minimum sample of 176 subjects is needed to detect a 15% difference in incidence of caries, with a significance level of 95% and a power of 80% [16]. The researchers decided to aim for doubling the effective sample size to 300 subjects to ensure the effective sample size will be higher than 176 with a high power. After taking sampling error into account and the assumption of a 30% nonresponse rate, followed by the assumption of another 30% of drop-out rate, a total of 600 subjects will be approached to participate in this study.

The kindergartens that agreed to participate will be randomly allocated into either the intervention or control group (1:1) by a random “draw” method. No matching will be done since they all have a similar socioeconomic background. All children aged 5 or 6 years at the participating kindergartens, with parents’ consent to participate, will be included in the study [17].

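### The 176 subjects and 80% power assume individually randomised children, but kindergartens are randomised and no design effect is applied, so the claimed high power is unsupported

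*Protocol article*

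**What the plan says.** All the figures are in the protocol article, Methods, Sample Size and Randomization. The planning assumption is that "there will be a 5% of incidence of caries in the intervention group during the follow-up"; the figure for the other arm is given as "compared with 20% in the control group". From this, "a minimum sample of 176 subjects is needed to detect a 15% difference in incidence of caries"; the error rates behind that number are worded as "with a significance level of 95% and a power of 80" per cent. The target is then raised: the researchers aim for "doubling the effective sample size to 300 subjects to ensure the effective sample size will be higher than 176 with a high power". The number to be approached follows from an "assumption of a 30% nonresponse rate, followed by the assumption of another 30% of drop-out rate, a total of 600 subjects".

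The next paragraph of that section allocates whole kindergartens 1:1 by a random draw and takes in every consenting child aged 5 or 6 in each one. The article states no ICC, design effect, cluster size or number of kindergartens. The only reason given for going from 176 to 300 is to stay above 176 with high power. Clustering is not mentioned, either there or in the Data Analysis section.

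**The concern.** Children at one kindergarten may resemble each other in caries risk, for instance through shared neighbourhood, diet or access to dental care. When kindergartens are randomised, that resemblance inflates the variance of the difference between arms by the design effect, 1 + (m − 1) × ICC, where m is the number of analysed children per kindergarten. A sample size computed for independent children then overstates the information in the trial. In this setting 300 analysed children amount to an effective 300 only if the ICC is zero.

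This is more than detail that a condensed article may leave to a fuller document. The article presents a finished calculation with a power attached, and that calculation does not match the unit of randomisation stated beside it. The affected outcome is the primary one, the number of children with new caries, which also feeds the cost per child prevented from developing caries. If the true power were well below the stated level, a null result could be read as evidence against home visits when it was only imprecise. A reader of the article cannot judge that risk.

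**Working it through.** **Inputs from the article:** incidences 0.05 and 0.20; 80% power; significance level written as 95%, read as α = 0.05 (sidedness is not stated; two-sided reproduces the figure); minimum 176; target 300; 600 approached; losses of 30% and then 30%.

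**Inputs that are assumptions:** ICC 0.01 to 0.10 and m = 10 to 30. The article gives neither.

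**Step 1. Reproduce 176.** With mean incidence p̄ = 0.125 and difference d = 0.15:

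- 1.960 × √(2 × 0.125 × 0.875) = 0.9167
- 0.8416 × √(0.05 × 0.95 + 0.20 × 0.80) = 0.3834
- n₀ = (0.9167 + 0.3834)² / 0.15² = 75.1 per arm without continuity correction (76, so 152 in total)
- With continuity correction: n = (n₀/4) × [1 + √(1 + 4/(n₀ × d))]² = 87.9, so 88 per arm and **176 in total**

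The match is exact. One-sided versions give 120, or 144 with the correction. So 176 is right for its inputs and contains no allowance for clustering.

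**Step 2. From 176 to 300 and 600.** 2 × 176 = 352, whereas 300/176 = 1.70, so the target is not a doubling. 600 × 0.7 × 0.7 = 294, which agrees with 300 to within 2%. That is rounding, and 294 is used below as the number analysed.

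**Step 3. Design effect that 294 can absorb.** 294/176 = 1.67. Setting 1 + (m − 1) × ICC = 1.67 gives the largest ICC that keeps 80% power:

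| m | largest ICC |
|---|---|
| 10 | 0.074 |
| 15 | 0.048 |
| 20 | 0.035 |
| 30 | 0.023 |

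**Step 4. Power with 294 analysed.** Let n = 147 / design effect per arm. On the same formula as the plan's 176,

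power = Φ{[d − 1/n − 1.960 × √(2p̄(1 − p̄)/n)] / √[(0.05 × 0.95 + 0.20 × 0.80)/n]}.

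Example, m = 20 and ICC 0.05: the design effect is 1 + 19 × 0.05 = 1.95 and n = 147/1.95 = 75.4. The numerator is 0.15 − 0.0133 − 0.1056 = 0.0312, the denominator is 0.0525, the ratio is 0.594, and power is 72%.

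| m | ICC 0.01 | ICC 0.02 | ICC 0.05 | ICC 0.10 |
|---|---|---|---|---|
| 10 | 95% | 93% | 86% | 74% |
| 15 | 94% | 91% | 79% | 61% |
| 20 | 93% | 88% | 72% | 51% |
| 30 | 90% | 83% | 60% | 36% |

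If clustering is ignored (design effect 1), the same formula gives 96%.

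**Step 5. The minimum itself.** Multiplying 176 by the design effect gives 192 analysed children at the favourable corner (m = 10, ICC 0.01; design effect 1.09) and 687 at the unfavourable corner (m = 30, ICC 0.10; design effect 3.90).

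**The case against.** The strongest defence is that the plan has margin. Going from 176 to about 294 absorbs a design effect of 1.67, and with small kindergartens or a low ICC power stays above 80%: at ICC 0.02 it is 83% or more for every cluster size in the table. The continuity correction is also conservative. Without it the base requirement is 152, the tolerated design effect is 294/152 = 1.93, and power at ICC 0.05 is 85%, 80% and 70% for 15, 20 and 30 children per kindergarten. The planned difference is cautious too. The cited study is reported as finding 4% versus 39%; at those rates the Step 4 formula gives about 94% even at ICC 0.10 and 30 per kindergarten.

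All of this stands, and it rules out a reading that a reader might be tempted to make, namely that the trial is underpowered. The documents do not show that, because the result turns on an ICC and a cluster size that they do not give. But the margin was not set with clustering in view, and the article does not plan on 4% versus 39%. Its remark that the kindergartens share a similar socioeconomic background is offered as the reason for not matching, and no ICC is derived from it.

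A reader might also infer that the whole chain 176, 300, 600 is miscalculated. It is not: 176 is exact for its inputs and 600 follows from 300 within rounding. Only the word doubling is wrong, and that slip is harmless in itself because 300 still exceeds the stated minimum.

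Finally, a full protocol may hold the number of kindergartens and an ICC. That would supply the missing inputs, but it would not make 176 at 80% power a correct statement for a cluster-randomised trial.

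**Conclusion.** The point holds in this form: 176 subjects with 80% power is a valid result for individually randomised children and is stated for a trial that randomises kindergartens. Describing 300 as an effective sample size with high power is therefore unsupported. The consequence could be negligible or serious. Under the assumed ranges, 294 analysed children give anything from about 95% to 36% power, and 80% is kept only while the design effect is at most about 1.67. These figures rest on equal cluster sizes, the usual design-effect formula and the continuity-corrected method that reproduces the plan's own number. The conclusion is that power is not established for this design, not that it is inadequate.

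**What to change.** Rewrite the sample size paragraph so that it:

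- gives the number of kindergartens, the expected number of analysed children in each, and an assumed ICC with a range (0.01 to 0.10 would be reasonable to show);
- multiplies 176 by 1 + (m − 1) × ICC and states the power that about 294 analysed children provide across that range;
- reserves the term effective sample size for the number after division by the design effect;
- replaces doubling with the actual factor (300 is 1.7 times 176).

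The cost is one paragraph and a stated power less favourable than the present wording suggests. No change to recruitment is required. Using more, smaller kindergartens would raise the effective sample size for the same number of children, but this is optional and not free: the article enrols all consenting children at each participating kindergarten and reports that recruitment is under way, so it would mean changing that rule or securing the agreement of further kindergartens.

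### The unrestricted draw of kindergartens rests on an unsupported claim of similarity; a draw within a few strata and adjustment for baseline caries would recover precision at little cost

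*Protocol article*

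**What the plan says.** In the Protocol article, Sample Size and Randomization, the unit of allocation is the kindergarten. Those that agree to take part are "randomly allocated into either the intervention or control group (1:1) by a random “draw” method". The same paragraph declines to restrict the draw: "No matching will be done since they all have a similar socioeconomic background". Every consenting child aged 5 or 6 in a participating kindergarten is enrolled.

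On the kindergartens themselves, Recruitment says "The population of interest is children aged 5 and 6 years from kindergartens in the Selangor state in Malaysia" and "The names and addresses of the kindergartens will be obtained from the OHD". Neither the number of kindergartens nor their split between rural and urban areas is given.

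On variation in caries, the Introduction reports for Malaysia that "86% of rural and 69% of urban preschool children have experienced dental caries".

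The planned effect is "5% of incidence of caries in the intervention group during the follow-up, compared with 20% in the control group". Under Outcome Measures, prevented cases are defined as the difference between groups in the number of children with new caries. Under Baseline Data, consenting children are examined for caries at the kindergarten. Data Analysis names a t test and a logistic regression on individual characteristics.

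**The concern.** The decision not to restrict the draw is stated together with its reason, so the reason can be judged. It is weak in two ways.

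- **It is unsupported.** No data are given, and the kindergartens are whichever ones in Selangor agree to take part.
- **It does not address what must balance.** The quantities that matter are caries risk and the number of children per kindergarten. Kindergartens of similar socioeconomic background can differ in both. The Introduction's own figures show a 17-point difference in caries experience by location.

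When whole kindergartens are drawn, a chance difference in risk between the arms shrinks with the number of kindergartens, not the number of children. What is at stake is precision and the face validity of the comparison. A second effect concerns size: a 1:1 draw of kindergartens need not give equal numbers of children, and the primary effect is defined as a difference in counts.

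**Working it through.** **Inputs.** From the protocol: rural 86% and urban 69% (Introduction); 5% against 20%, a 15-point effect, and a target of 300 children (Sample Size and Randomization). Assumed, because not stated: K kindergartens of equal size, K/2 per arm, a share p of them rural, and a rural-urban gap g in two-year incidence.

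**1. The plan's own figure.** The protocol says "a minimum sample of 176 subjects is needed to detect a 15% difference in incidence of caries". With two-sided alpha 0.05 and 80% power, the uncorrected formula gives 1.690 / 0.15² = 75.1, so 76 per arm (152 in total). With the continuity correction, (75.1/4) × [1 + √(1 + 4/(75.1 × 0.15))]² = 87.95, so 88 per arm. The total is 176, which reproduces.

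**2. Chance difference from location.** Under a simple draw the number of rural kindergartens in one arm is hypergeometric. The difference between arms in rural share has SD = 2√[p(1−p)/(K−1)], and the resulting difference in outcome has SD = g times that. With p = 0.5 this reduces to g/√(K−1). With g = 17:

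- K = 4: 17/√3 = 9.8 points
- K = 6: 17/√5 = 7.6 points
- K = 10: 17/√9 = 5.7 points
- K = 20: 17/√19 = 3.9 points
- K = 40: 17/√39 = 2.7 points

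With p = 0.2 the SD is 4.5 points at K = 10 and 3.1 at K = 20. For scale, the sampling error of the difference with 150 independent children per arm is √[(0.05×0.95 + 0.20×0.80)/150] = 3.7 points.

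**3. From prevalence to incidence.** The 17 points are a difference in prevalence. Rescaling the rural-urban contrast to a mean incidence of 20%, half rural, gives:

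| Contrast held constant | Incidence, urban and rural | Gap g | SD, K = 10 | SD, K = 20 |
|---|---|---|---|---|
| 17 points unchanged | 11.5% and 28.5% | 17 | 5.7 | 3.9 |
| Odds ratio 2.76 | 12.2% and 27.8% | 15.5 | 5.2 | 3.6 |
| Cumulative hazard ratio 1.68 | 15.4% and 24.6% | 9.1 | 3.0 | 2.1 |
| Risk ratio 1.25 | 17.8% and 22.2% | 4.4 | 1.5 | 1.0 |

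The unchanged 17-point gap is therefore the upper end of this range.

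**4. How often it would be large.** With p = 0.5 and g = 17, a 15-point imbalance needs rural shares that differ by 15/17 = 88 percentage points. For K = 4 to 10 that means complete separation of the arms, with these probabilities:

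- K = 4: 2/6 = 33%
- K = 6: 2/20 = 10%
- K = 8: 2/70 = 2.9%
- K = 10: 2/252 = 0.8%

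At K = 20 or more the probability of 15 points is practically 0. An imbalance of at least 7.5 points, half the planned effect, has probability 52/252 = 21% at K = 10 and 4252/184756 = 2.3% at K = 20. If only 20% to 25% of kindergartens are rural and are split as unevenly as possible, the largest imbalance is 2p × 17 = 6.8 to 8.5 points, so 15 cannot be reached.

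**5. Size.** Suppose, as an illustration, 20% incidence in both arms and 180 control against 120 intervention children. The difference in counts is 36 − 24 = 12 children with no effect at all. The planned effect with 150 per arm is 30 − 7.5 = 22.5 children. As proportions the first case gives 20% − 20% = 0.

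**The case against.** The case on the other side is substantial, and much of it stands.

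- **The 86% and 69% are national lifetime prevalence.** They are not two-year incidence in Selangor, and nothing says that both rural and urban kindergartens will be drawn. This stands. It is why the figures above are conditional and the rescaled gaps are shown.
- **Location is not socioeconomic background, so the two statements do not strictly contradict each other.** This also stands. The point is that the stated reason is unsupported and insufficient, not that the Introduction disproves it.
- **An unrestricted draw of clusters is a valid design.** Chance imbalance adds variance, which an analysis by kindergarten takes into account. This stands, and it limits the point to precision. The analyses named in the article include no location, baseline-caries or kindergarten term. A fuller plan may contain one, so that omission is not counted as a fault here.
- **Unequal numbers of children are cured by proportions, whatever the draw.** Correct, and the fix says so.
- **With few kindergartens, crossing two factors leaves strata of two or three.** Correct. The strata must be kept few.

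A reader might infer from 17 points against 15 that imbalance could match the planned effect. The documents do not support that. It would need nearly complete separation of the arms by location, very few kindergartens and a gap in incidence close to the full prevalence gap. None of these is stated.

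**Conclusion.** The similarity statement does not justify an unrestricted draw. It has no data behind it and bears on neither caries risk nor kindergarten size. The cost is lost precision and chance imbalance. With half the kindergartens rural and the full gap carried over, a typical (1 SD) imbalance is 5.7 points with 10 kindergartens and 3.9 with 20, which is 38% and 26% of the 15-point effect. With smaller incidence gaps it falls to between 1.0 and 5.2 points, and it is also smaller when few kindergartens are rural. These sizes rest on an assumed number, mix and equal size of kindergartens. There is no systematic bias, and an imbalance as large as the planned effect is unlikely. The change is worth making because it is cheap, not because the design is invalid.

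**What to change.** 1. Delete the similarity justification, and state the number of kindergartens.
2. For kindergartens not yet drawn, keep the drawing of lots but do it within a small number of strata. Use one factor, baseline caries prevalence or location, and add kindergarten size only if the number of kindergartens allows. Hold the draw after consent forms are returned and the baseline examination is done, so that the factor is known and allocation cannot influence consent.
3. Recruitment is already under way, so leave any allocation already made as it is.
4. For all kindergartens, adjust the primary comparison for baseline caries and the stratification factor, in an analysis that respects kindergarten.
5. Express the primary effect as a difference in proportions, so that unequal numbers of children per arm do not enter it.

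**Cost:** some protocol wording and a few sets of lots instead of one. The draw waits for baseline data that are collected anyway, and the model carries one or two more terms.
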